## Abstract

**Background:**

The number of obese children in the US remains high, which is problematic due to the mental, physical, and academic effects of obesity on child health. Data indicate that school-age children, particularly underserved children, experience unhealthy gains in BMI at a rate nearly twice as fast during the summer months. Few efforts have been directed at implementing evidence-based programming to prevent excess weight gain during the summer recess.

**Methods:**

Camp NERF is an 8-week, multi-component (nutrition, physical activity, and mental health), theory-based program for underserved school-age children in grades Kindergarten - 5th coupled with the USDA Summer Food Service Program. Twelve eligible elementary school sites will be randomized to one of the three programming groups: 1) Active Control (non-nutrition, physical activity, or mental health); 2) Standard Care (nutrition and physical activity); or 3) Enhanced Care (nutrition, physical activity, and mental health) programming. Anthropometric, behavioral, and psychosocial data will be collected from child-caregiver dyads pre- and post-intervention. Site-specific characteristics and process evaluation measures will also be collected.

**Discussion:**

This is the first, evidence-based intervention to address the issue of weight gain during the summer months among underserved, school-aged children. Results from this study will provide researchers, practitioners, and public health professionals with insight on evidence-based programming to aid in childhood obesity prevention during this particular window of risk.

**Trial Registration:**

NCT02908230/09-19-2016

## Background

While recent reports indicate a plateau in the rate of childhood obesity in the United States, the number of obese children remains high [1]. In 2011–2012, obesity affected 17 % of US youth, with 31.8 % being classified as overweight or obese [1]. Significant differences in prevalence of obesity exist between racial, ethnic and age groups. Non-Hispanic black and Hispanic youth are significantly more affected by obesity than their non-Hispanic White and non-Hispanic Asian peers [1]. Additionally, there appears to be a developmental trajectory in prevalence of obesity as 8 % of 2- to 5-year olds, 17.7 % of 6- to 11-year olds, and 20.5 % of 12- to 19-year olds were classified as obese in 2011–2012 [1]. So while it appears that the rise in obesity has tapered off, the prevalence of overweight and obesity among US youth remains concerning due to its devastating consequences, which affect the physical and mental health of children, as well as their academic success [2, 3].

Emerging research has begun to point to particular windows of risk for child weight gain. Troubling data indicate that school-age children experience unhealthy gains in BMI at a rate nearly twice as fast during the summer months when school is out of session compared to the school year [4–10]. African American and Hispanic, minority groups and economically disadvantaged children, subpopulations already at increased risk for obesity, as well as girls, may be particularly vulnerable to unhealthy weight gain during these non-academic months [1]. Limited knowledge of the external factors that lead to altered diet and physical activity during the summer time is available to adequately explain the unfavorable weight gain occurring in many children during this window of risk [11].

The rise and current status of obesity in the US has occurred at such a rapid rate that it cannot solely be attributed to biological changes [12]. While obesity rates have been rising over the past several decades, the US food environment has also been changing drastically, providing convenient access to an abundance of inexpensive, highly palatable, energy-dense foods [13]. Thus, the current prevalence of childhood obesity and demonstrated increase in obesity during the summer months could be a response to children’s increased exposure to the food environment [13], which they have less frequent access to during the school year, and lack of structured physical activity. Schools play a critical role in promoting healthy diet and physical activity behaviors during the academic year [14]. During the summer months, however, children lose access to this structured environment (e.g., provision of healthy snacks and meals; opportunity for structured and unstructured physical activity; nutrition, physical activity, and health related policies and programs).

The United States Department of Agriculture (USDA) aims to provide access to healthy, nutritious meals to children during the summer months through the USDA Summer Food Service Program (SFSP) [15]. Unfortunately, attendance at USDA SFSP sites, especially open sites, and amount of meals served tends to be low. According to the Food Research Action Center, only 15.8 % of free or reduced-cost school lunch participants received lunch in the summer of 2015 nationally [16]. In Ohio, only 10.8 % of free or reduced-cost school lunch participants participated in the SFSP [17]. Several stakeholders have hypothesized that these low numbers are due to a lack of structured programming at the sites to attract children. Few efforts have been directed at designing evidence-based nutrition and physical activity programs to equip underserved children with the necessary knowledge, skills, and other resources to prevent excess weight gain during the summer recess.

Camp Nutrition Education Recreation and Fitness (NERF) is a multi-component, evidence-based nutrition, physical activity, and mental health intervention that is coupled with USDA SFSP open sites in Columbus, Ohio. To our knowledge, this is the first multi-component, evidence-based intervention to address the disproportionate childhood weight gain in underserved children during the summer months. The long-term goal is to develop and implement effective theory-based community nutrition and physical activity interventions for childhood obesity prevention, particularly in underserved minority children, aimed at empowering children to make healthy dietary and physical activity choices and achieve a healthy weight and, ultimately, overall optimal health and wellness. The primary aims of this research project are to:Evaluate the efficacy of Camp NERF to improve child nutrition, physical activity, mental health, and anthropometric outcomes.Hypothesis 1.1: Diet quality, physical activity and sedentary time, positive and negative affect, BMI z-scores, and waist circumference (WC) z-scores will improve more from baseline to post-intervention among children participating at the Enhanced Care sites compared to Standard Care and Active Control sites.
Evaluate the efficacy of Camp NERF to improve caregiver self-efficacy for establishing healthy family nutrition and physical activity practices, amount of physical activity, and BMI.Hypothesis 2.1: Caregiver self-efficacy scores for establishing healthy family nutrition and physical activity practices, physical activity score, and BMI will improve more from baseline to post-intervention among families participating at the Enhanced Care sites compared to the Standard Care and Active Control sites.
Evaluate the efficacy of Camp NERF to improve youth mentor nutrition, physical activity, and anthropometric outcomes.Hypothesis 3.1: Diet quality, physical activity and sedentary time, positive and negative affect, BMI z-scores, and waist circumference (WC) z-scores will improve among youth mentors from baseline to post-intervention.

## Methods

### Camp NERF theoretical framework

Commonalities among the relatively few successful community-based childhood obesity prevention efforts include: theoretical framework to the intervention, multi-component strategies, direct or indirect engagement of caregivers, and specific behavioral targets [18]. It has become widely accepted that use of a theoretical framework in the design of behavior change interventions is an essential ingredient for achieving positive outcomes. The Camp NERF intervention is guided by the social ecological model (SEM) and social cognitive theory (SCT) [19–21].

According to the socio-ecological framework, there is a complex interplay of factors at multiple levels of influence that determine a child’s weight status, health, and wellness [22]. A child’s risk for obesity is influenced by personal factors, such as genetics and diet and physical activity behaviors. These personal factors are, in turn, influenced by multiple external layers of influence including caregiver/family practices and behaviors, environmental settings (home, school, community), various organizational sectors (education, government, public health, leisure, recreation), and social norms and values (societal rules that guide attitudes, beliefs, and behaviors, peer influence). The socio-ecological framework provides a theory-based approach to investigating the problem of childhood obesity and an understanding of the deep complexity of the etiology of this disease. It also serves as a useful tool in the design of theory-based behavior change interventions – and underlines the necessity in conducting cross-disciplinary research to effectively diminish the problem of childhood obesity.

The SCT broadly used among community nutrition researchers, proposes that behavior change results from a reciprocal relationship between personal and external factors [20]. An individual needs the personal resources to enact the desired behavior, which includes: knowledge and skills (ability to perform desired behavior); cognitive behavior techniques (goal-setting, problem solving, coping strategies); and self-efficacy (confidence in one’s ability to enact the behavior). Regarding cognitive behavioral techniques, self-control is achieved via goal-setting. When goals are not achieved, alternative skills, such as problem solving and coping strategies can be employed to attain initial goals or set new, more achievable goals [20]. Also worth noting, children and adolescents who develop proficiency in general cognitive behavior techniques experience a sense of personal empowerment. In turn, this alleviates the mental health symptoms associated with overweight and obesity (poor self-concept and symptoms of anxiety and depression), leading to subsequent diet and physical activity related behavior change [23]. Cognitive behavior techniques are either vastly underdeveloped or missing from the curriculum of most childhood obesity prevention interventions [24, 25]. The Camp NERF intervention utilizes two evidence-based curricula that incorporate cognitive behavioral techniques - Coordinated Approaches to Child Health (CATCH) [26] and Creating Opportunities for Personal Empowerment (COPE) [27]. Additionally, goal-setting opportunities strategies are integrated into the Camp NERF curriculum and achievement of goals are tracked with goal-setting necklaces.

Under the SCT, environmental or external factors also play a part in determining behavior. With regards to child diet and physical activity behaviors, examples include: role modeling (caregivers, teachers, peers), availability of healthy meals and snacks, opportunity for indoor or outdoor physical activity and structure provided by daily routines [22]. Due to the complexity of behavior origination and change, the most efficacious interventions have been multi-component in design and included either direct or indirect caregiver engagement. As the nutritional gatekeepers of the household, caregivers play a major role in shaping the eating behaviors of their children and thus must be included as an intervention target [28]. Caregivers help children establish and reinforce target behaviors by role modeling intake of healthy foods, setting expectations for healthy food intake, and making healthy foods available [29]. The same principle holds true for physical activity related behaviors – that is, caregivers heavily influence their child(ren)’s engagement in physical activity and exercise, as well as sedentary and screen time [30]. Thus, caregivers must be involved either directly or indirectly in behavioral interventions directed at the child. The food and physical activity environments, caregivers, and peers are all targets of the Camp NERF intervention.

In sum, due to the inherent complexity of behavior, use of theoretical frameworks, such as the SEM and SCT, are absolutely critical in the design and conduct of behavioral interventions. Please refer to Fig. 1 for the Camp NERF theoretical framework.

**Fig. 1 Fig1:**
[figure not shown]
Camp NERF 2015 Theoretical Framework

### Research design

Camp NERF is an 8-week pre-test, post-test group site-randomized controlled trial. It is a multi-component nutrition, physical activity, and mental health education intervention coupled with the USDA SFSP, specifically open sites located at public elementary schools. Through daily access to healthy foods, safe play and structured physical activity, along with engagement in an evidence-based health behavior educational curriculum, Camp NERF is designed specifically to prevent unintended, unhealthy weight gain during the summer months in underserved school-aged children. Potential sites were identified by a community partner whose responsibility it is to support SFSP sites in Franklin County, OH, and were considered eligible if they were: 1) an elementary school; 2) a USDA SFSP open site; and 3) lacking structured programming. Twelve sites were identified as meeting these inclusion criteria and will be randomized to one of three treatment or programming groups: 1) Enhanced Care (nutrition, physical activity, and mental health programming); 2) Standard Care (nutrition and physical activity programming); and 3) Active Control (non-nutrition, physical activity, and mental 4H programming). Figure 2 provides an overview of the three treatments for Camp NERF.

**Fig. 2 Fig2:**
[figure not shown]
Overview of the Camp NERF Treatments

Power was calculated using change in BMI z-score as the outcome of interest. Based on the results from previous pilot test [31, 32], we assume that between-subject variation is normally distributed with a standard deviation of 1.03 and that between-site variation (nested within treatment group) is negligible. Under these assumptions, recruiting 20 subjects per site (planning for 20 % attrition) provides approximately 70 % power to detect a difference of 0.5 points in change in BMI between the treatment group and either of the two control groups using a one-sided test at alpha = 0.05. The model used is described further in the Data Analysis section.

USDA SFSP open feeding sites operate 5 days a week from mid-June through the beginning of August. Their hours of operation will be approximately 9:00 AM – 3:00 PM, although these times vary slightly by site. Camp NERF program (Enhanced Care, Standard Care, or Active Control) will occur 2 days per week for approximately 4 hours each day. This is expected to equate to 64 h of direct exposure per child, a sufficient dose for eliciting behavior change in the targeted outcomes [33–42]. Table 1 provides an overview of a sample day at an Enhance Care site.

**Table 1 Tab1:** Camp NERF daily curricula delivery schedule at enhanced care sites

Time	Grades K-2	Time	Grades 3–5
8:30 AM	Arrival; Engage with participants before and during breakfast	8:30 AM	Arrival; Engage with participants before during breakfast
10:00 AM	Nutrition Education	10:00 AM	Physical Education
10:00 AM	Discussion	10:00 AM	*Warm-up*
10:10 AM	*Learning Activity*	10:05 AM	*Go Fitness*
10:25 AM	*Physical Activity*	10:20 AM	*Go Activity*
		10:40 AM	*Cool-down*
10:45 AM	Mental Health	10:45 AM	Mental Health
11:15 AM	Physical Education	11:15 AM	Nutrition Education
11:15 AM	*Warm-up*	11:15 AM	Discussion
11:20 AM	*Go Fitness*	11:25 AM	*Learning Activity*
11:35 AM	*Go Activity*	11:40 AM	*Physical Activity*
11:55 AM	*Cool-down*		
12:00 PM	Lunch; Lunchtime Engagement and Trivia	12:00 PM	Lunch; Lunchtime Engagement and Trivia

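### The stated power of about 70% does not follow from the inputs printed with it, which give about 78% to 86% for one comparison with 64 completers per arm

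*Protocol article*

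**What the plan says.** All the ingredients are in the protocol article, under Methods, Research design. The power paragraph follows the Fig. 2 caption.

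- Outcome: "Power was calculated using change in BMI z-score as the outcome of interest".
- Variability: "between-subject variation is normally distributed with a standard deviation of 1.03", with the further assumption that "between-site variation (nested within treatment group) is negligible".
- Sample: "recruiting 20 subjects per site (planning for 20 % attrition".
- Target: "power to detect a difference of 0.5 points in change in BMI between the treatment group and either of the two control groups".
- Result: approximately 70% power.
- Test: one-sided, at the 5% level.
- Sites: "Twelve sites were identified as meeting these inclusion criteria and will be randomized to one of three treatment or programming groups".

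The paragraph refers to the Data analysis section for the model. That section describes a mixed effects linear regression with between-site and within-site variability. It prints no other significance level and no multiplicity rule.

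**The concern.** This is the only sample-size justification in the article, and it prints every number needed for a check. Since between-site variation is taken as negligible, the calculation reduces to a comparison of two means, so a reader should be able to recover the stated power closely. If the result cannot be recovered, either a printed number is wrong or an input that drives the result is not printed.

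The possible explanations have different consequences. If the power is misprinted, the trial has more power on its own assumptions than it claims. If the calculation used a stricter level or a both-comparisons criterion, the rule for judging Enhanced Care against Standard Care and Active Control (Hypothesis 1.1) is not the one printed. If 1.03 is not the standard deviation of change, the precision of the main comparison is not what the sentence implies. It is better to settle this before results are reported.

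**Working it through.** **Inputs.** From the power paragraph: difference 0.5, SD 1.03, between-site variance zero, 20 recruited per site, 20% attrition, one-sided alpha 0.05. From Research design: 12 sites and 3 groups.

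**Assumptions, not stated in the article.**
- Sites split equally, 4 per arm.
- 1.03 is the SD of the change score.
- 0.5 and 1.03 are on the same scale.

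**Numbers per arm.** Recruited: 4 × 20 = 80. Completing: 80 × 0.8 = 64.

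**Attempt to reproduce the stated 70%.**

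Standard error of the difference = 1.03 × √(2/64) = 0.1821.

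Standardised difference = 0.5 / 0.1821 = 2.746.

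Normal approximation: Φ(2.746 − 1.645) = Φ(1.101) = 0.865.

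The t versions use a noncentral t with noncentrality 2.746. With 80 analysed per arm (20 per site taken as the number after attrition), the standard error is 1.03 × √(2/80) = 0.1629 and the standardised difference is 3.070.

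| Reference distribution, one-sided 0.05 | Critical value | Power, 64 per arm | Power, 80 per arm |
|---|---|---|---|
| Normal | 1.645 | 86.5% | 92.3% |
| t, subject-level df (126; 158) | 1.657; 1.655 | 86.1% | 92.1% |
| t, 9 site-level df (12 sites − 3 arms) | 1.833 | 81.2% | 88.2% |
| t, 6 site-level df (8 sites − 2 arms) | 1.943 | 78.1% | 85.5% |

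The lowest entry is 8 points above the stated figure, so rounding does not explain the gap.

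**What 70% would imply at the stated test (normal approximation).**
- Children per arm: 2 × (1.03/0.5)² × (1.645 + 0.524)² = 39.9, about 40, against 64 or 80.
- Detectable difference at 64 per arm: 0.1821 × (1.645 + 0.524) = 0.395, against 0.5.

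**Unstated ingredients that do give about 70%.**

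| Changed ingredient | Power |
|---|---|
| One-sided 0.025 per comparison, 9 df (critical value 2.262), 64 per arm | 68.7% |
| Dunnett adjustment for two comparisons, 9 df, 64 per arm (simulated) | 71.3% |
| Winning both comparisons, each at one-sided 0.05, 9 df, 64 per arm (simulated) | 71.3% |
| 1.03 as a single-visit SD, visits uncorrelated, 80 per arm, normal approximation | 70.1% |

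For the last row, the change SD is 1.03 × √2 = 1.457, the standard error is 1.457 × √(2/80) = 0.2303, the ratio is 0.5/0.2303 = 2.171, and Φ(2.171 − 1.645) = 0.701. With 64 per arm the same reading gives 61.7%.

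At 64 per arm and one-sided 0.05 (normal approximation), 70% would also follow from an intraclass correlation of about 0.04. That contradicts the stated assumption of negligible between-site variation.

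**The case against.** The strongest reply is that the printed alpha and the printed power may both be right, with the calculation described incompletely. The text calls 1.03 a between-subject standard deviation and never says it belongs to the change score. Hypothesis 1.1 expects Enhanced Care to do better than both other groups, so power to win both comparisons is a possible target, although the words "either of the two control groups using a one-sided test at alpha = 0.05" more naturally describe each comparison separately. A strongly unequal split of sites could also come near 70%: with 2 sites against 5 and 9 df it is 69%. In addition, an article condenses a fuller plan, where degrees of freedom and multiplicity handling usually sit.

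Much of this stands. A reader might infer that alpha was meant to be one-sided 0.025, because that level with 9 df gives 68.7%. The document does not support that inference, since several other ingredients come as close or closer and nothing in the text chooses among them. A reader might also infer that the trial is too small. The arithmetic points the other way on the printed inputs.

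The reply does not remove the mismatch. This is not a complaint that detail has been left out: the article prints a set of inputs and a result, and they disagree. Each rescue has to add or change an input that the sentence does not give.

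**Conclusion.** The point holds as a failure of the stated inputs to give the stated result. For one pairwise comparison at one-sided 0.05, power is about 86% (subject-level df), 81% (9 df) or 78% (6 df) with 64 completers per arm, and 85% to 92% with 80 analysed. The stated value is about 70%, a gap of 8 to 22 points. This rests on an equal split of sites, on 1.03 being the SD of change, and on the article's own assumption of no between-site variation.

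Confidence is high that the figure does not reproduce on the plain reading. The cause cannot be settled from the document, so neither the alpha nor the power can be named as the misprint. Severity is should-fix, because the printed figure is conservative on its own inputs.

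**What to change.** Correct the power sentence so that its inputs and result agree.

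- If the printed inputs stand (1.03 is the SD of change; one-sided 0.05 for each comparison), restate the power as about 81% with 9 site-level df, or about 86% with subject-level df. Say which was used and that it assumes zero between-site variation.
- If 70% came from a different alpha, a multiplicity adjustment, a both-comparisons criterion or a different SD, print that input and use the same alpha and criterion in the analysis.

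In either case, say whether 20 per site is before or after attrition, because the answer moves the result by several points. The replacement figure should come from the authors' own calculation once these inputs are confirmed. The cost is a recalculation and a sentence or two of text, with no change to sites or enrolment.

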### Participants and recruitment

The target population for Camp NERF is underserved minority children entering kindergarten through fifth grade and their adult caregiver from urban neighborhoods in Columbus, Ohio. Participants will be recruited through a variety of methods including, but not limited to, school announcements, emails, flyers, phone calls, and neighborhood canvassing. Prior to enrollment in the study, a consent form, parental permission form, and assent form will be completed by the caregiver and child, respectively.

Also, data will be collected from high school students who will serve as Youth Mentors for the child participants at the Camp NERF Enhanced Care sites. The Youth Mentors will be recruited through a collaborating partner, the Godman Guild Association that provides internships to high-school aged students during the summer months through Temporary Assistance for Needy Families (TANF) funding. Prior to study enrollment, a parental permission form and assent form will be completed by the caregiver and Youth Mentor, respectively, for those under the age of 18. Youth Mentors 18 years of age or older will complete consent forms prior to enrollment in the study. Individuals who are not interested in enrolling in the study will still be able to participate as Camp NERF Youth Mentors.

